## Methods: monitoring

### Trial management

The Sponsor of the trial is the University of Southampton. ATTACK is managed from a central Trial Coordinating Centre based at the University of Nottingham. The Southampton CTU will support all statistical processes, including ongoing central statistical monitoring and preparation of open and closed trial reports, randomisation design, set-up and support.

A Trial Steering Committee (TSC) provides overall supervision on behalf of the Sponsor and Funder and ensures that the project is conducted to the rigorous standards set out in the Department of Health’s Research Governance Framework for Health and Social Care and the Guidelines for Good Clinical Practice. The Chair and members have been appointed by the NIHR Health Technology Assessment (HTA) Programme Director according to standard procedures. TSC meetings will have a minimum of 75% majority of independent members, including the Chair. Details of the terms of reference for the TSC are available on request from the ATTACK trial office.

A Data Monitoring and Ethics Committee (DMEC) will monitor unblinded comparative data, supplied in strict confidence, and make recommendations to the TSC on whether there are any ethical or safety reasons why the trial should not continue, ensuring that the safety, rights and well-being of the trial participants are paramount. The DMEC comprises a statistician and two clinicians with expertise in the clinical area. All members are independent and have been appointed by the NIHR HTA Programme Director according to standard procedures. Details of the terms of reference for the DMEC are available on request from the ATTACK trial office.

### Data monitoring

Safety will be closely assessed throughout the trial. The absolute and relative risks of major bleeding will be examined by the DMEC and compared with those expected from the literature. All-cause mortality and the primary event rate will also be studied in order to determine net benefit, i.e. benefits minus harms. Aspirin use requires a consideration of the balance of risk vs. benefit in all populations. The DMEC will recommend termination of the trial if, in their view, the randomised comparisons provided have proven beyond reasonable doubt that the level of harm is unacceptable; or the use of aspirin is clearly contraindicated (or clearly indicated) in terms of the net effects. Clinical judgement will be required in interpreting the results of interim analyses and reaching recommendations. The DMEC will consider whether the evidence meets standards for treatment recommendations and practice guidelines, mindful that less evidence should be required to stop the trial for harm than benefit given the primacy of patient safety [94]. The absolute number of major bleeding events during ATTACK is likely to be low, and therefore, the confidence levels around any estimates of absolute and relative risk will be initially wide but narrow throughout the course of the trial. Hazard ratios may be unstable and drift over time into marginal levels of significance. Multiple “looks” at the data may give rise to a transient “signal” of benefit or harm [95]. Therefore, criteria of proof beyond reasonable doubt cannot be specified precisely, but in general, a difference of at least three standard deviations in an interim analysis of a major endpoint would be needed to justify halting, or modifying, such a study prematurely, especially for a comparison based on relatively few events (< 100) [96].

There are other instances where the DMEC may consider it advisable to advise termination of the study: flaws in design or conduct of the study come to light; or external new information on the treatment becomes available; or resources are inadequate to complete the trial.

### Interim analyses

#### Internal pilot

The first 24 months of the study (9 months set up and 15 months recruitment) are planned as an internal pilot. The key objective of the pilot is to assess GP and patient recruitment. Additional objectives are to finalise major event assessment procedures, monitor safety and assess fidelity to allocated group and patient withdrawal rates. The timings of the pilot period and interim analyses are subject to change if major contextual events impact on trial progress. This was evident in 2020–2021 when recruitment was held as a result of the SARS-Cov-2 pandemic.

##### GP and patient recruitment

Data will be provided on the number of practices overall, and by area, that indicate willingness to take part, perform eligibility assessment and start patient recruitment. The number (and percent per list size) of eligible patients per practice and the number and percentage of eligible patients willing to participate and commencing the trial will be recorded. At the end of the pilot phase, traffic light criteria will be used to establish whether the trial should continue without modification (green); study recruitment strategy changes are required (amber); or the trial should discontinue (red).

##### Endpoint assessment procedures

The adjudication process will be explored and refined during the pilot. Hospital discharge summaries will serve as the primary source of potential endpoint events. These will be assessed and categorised into clear major event or no event, or more information required. In the latter situation, the feasibility, value and costs will be explored of obtaining specific additional information from the original hospitalisation such as ECGs, CT scan results, photocopied medical notes to assess symptoms and post mortem results if in-hospital death. Events that are uncertain will be reassessed using whatever additional information can be obtained.

##### Safety

The plan is to assess safety after 15 months of recruitment (and allowing 3 months for report writing) from any bleeding events requiring hospitalisation in both arms using coded GP data, HES data, healthcare professional-/self-reporting and any other serious adverse event (SAE). This early review will be based on unadjudicated data due to the anticipated delay in receiving HES data. If the DMEC have concerns that fall short of “beyond reasonable doubt” on the basis of the unadjudicated data they will also have the option to halt the trial pending a process of formal adjudication.

##### Fidelity

Fidelity to allocated group by will be studied by examining repeat prescribing data from GP systems and the results of follow-up questionnaires in those reaching 12 months after recruitment.

##### Withdrawal

Withdrawal will be reported as the number (%) of patients who withdraw from the study and refuse access to linked routine data.

#### Subsequent interim analyses

It is anticipated that the DMEC will subsequently review unblinded data: after 24 months recruitment using non-adjudicated data (allowing 3 months for report writing); after 27 months recruitment using adjudicated data (allowing 9 months for adjudication and report writing); and at annual intervals thereafter using adjudicated data, or more frequently if specified by the DMEC.

#### Estimation of event rate

A confidential report to the DMEC on adjudicated major CVD events and bleeding events (by arm) is planned at 45 months into the study based on 27 months of actual recruitment (estimated 23% of primary endpoint events, 226 in the control arm).

Data on adjudicated major CVD events and bleeding events (overall, not by arm) will be reviewed by the TSC at its regular meetings. The TSC will have the option of increasing the sample size or prolonging the scheduled treatment period if the event rate is substantially lower than anticipated.

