### Sample size

A total of 25,210 patients (12,605 per arm) will be required in order for the required 1827 major vascular events to be observed.

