#### Definitive sample size estimate (accounting for competing risks)

As the primary outcome measure involves competing risks (deaths from other causes, including deaths from fatal bleeding which are anticipated to be higher in the aspirin arm), a sample size adjustment calculated using the Cumulative Incidence approach is required as recommended by Pintilie and Tai [80, 81]. Methods to calculate the sample size in the presence of competing risks [80, 81] were used under the following assumptions:
Proportional hazards assumption holds between the two armsA 2% annual major vascular event rate in the usual care armAn initial HR of 0.868 (equivalent to a 1.74% annual major vascular event rate in the aspirin arm)A 1.8% annual event rate in the usual care arm for deaths from other causes (including fatal bleeding)A 1.85% annual event rate in the aspirin arm for deaths from other causes (including fatal bleeding), i.e. assuming that patients in the aspirin arm will experience a 0.05% annual rate increase of fatal bleeding compared to patients in the usual care arm85% power, 5% two-sided alpha, 1% dropout rate3.5-year recruitment period and 2.5-year follow-up period

The corresponding sample size information was calculated as follows (all values rounded to 4 decimal places):
Cumulative incidence at 5 years (in the presence of competing risks) for the usual care arm of 0.0911Cumulative incidence at 5 years (in the presence of competing risks) for the aspirin arm of 0.0796Subdistribution HR of 0.8692Proportion of main event failures in the usual care arm of 0.0782Proportion of main event failures in the aspirin arm of 0.0682Pooled proportion of main event failures of 0.0732Number of major vascular events required of 1827Number of patients required (prior to an allowance of dropout) of 24,958Number of patients required (after an allowance of dropout) of 25,210 (12,605 per arm)

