As the event rate will be highly dependent upon the age and CKD severity of patients recruited, the age distribution and CKD stage of participants will be closely monitored during the first phase of the pilot in advance of the formal estimation of the control event rate, which will take place during the second phase. This will allow time to titrate the number of practices according to the recruitment rate per practice and top up our practice numbers in anticipation of a lower event rate, and to focus recruitment on more severe CKD, thereby enriching the ATTACK population with people at higher risk, should the trial population be younger than expected.

A report to the DMEC on adjudicated major CVD events and bleeding events (by arm) is planned for 45 months into the study based on 27 months of actual recruitment (estimated 23% of primary endpoint events, 226 in the control arm). Advice will be sought from the Trial Steering Committee (TSC) should the event rate differ significantly from that anticipated**.** The time points for this review may change if there are major contextual events that influence trial recruitment and/or progress.

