## Methods: assignment of interventions

### Allocation

Consenting patients will be randomised (open label randomisation) 1:1 via an independent web-based system (TENALEA) using random-block size, to GP prescription of aspirin vs no additional treatment (and avoidance of aspirin), stratified by age, diabetes and CKD severity. The randomisation system is run by the ALEA^TM^ team in Southampton and monitored and checked by the Southampton Clinical Trials Unit (CTU). The Regional Centres will enrol participants and assign to the intervention.

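### The 226 control-arm events (23% of the total) forecast for the 27-month event-rate review do not follow from the plan's own design assumptions, which give about 177 to 182 (18-19%)

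*Protocol article*

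**What the plan says.** The forecast appears twice in the protocol article, under Estimation of vascular event rate (Sample size) and under Estimation of event rate (Interim analyses). Both places put a by-arm report on adjudicated events to the DMEC at month 45, "based on 27 months of actual recruitment (estimated 23% of primary endpoint events, 226 in the control arm".

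The timing is set elsewhere. Subsequent interim analyses schedules this look "after 27 months recruitment using adjudicated data (allowing 9 months for adjudication and report writing". Internal pilot gives the set-up period: "The first 24 months of the study (9 months set up and 15 months recruitment) are planned as an internal pilot".

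The design assumptions are under Sample size. "A total of 25,210 patients (12,605 per arm) will be required" to yield 1827 events, with 3.5 years of recruitment and 2.5 years of further follow-up. Annual major vascular event rates are 2% in usual care and 1.74% on aspirin. For competing deaths the article assumes "A 1.8% annual event rate in the usual care arm for deaths from other causes" and "A 1.85% annual event rate in the aspirin arm for deaths from other causes". Allocation is equal: "Consenting patients will be randomised (open label randomisation) 1:1".

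As to use, the trial will seek TSC advice if the event rate departs materially from expectation. The TSC, which sees events overall and not by arm, may enlarge the trial or lengthen treatment if the rate is well below what was anticipated.

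**The concern.** The two stated figures agree with each other but look too high for a cut at 27 of 42 recruitment months. By then 27/42 = 64% of patients have entered, with a mean follow-up of 27/2 = 13.5 months. The full design runs to month 72 after the first entry.

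What is at stake is how the first adjudicated event-rate review is read. The article gives no other expected event count for it. Someone who sets the observed count beside 226 would see a shortfall in a trial that is exactly on plan. Someone planning the information available at that look would overstate it by about a quarter.

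**Working it through.** **Inputs** (Sample size, Internal pilot, Subsequent interim analyses): 12,605 per arm; event hazards 0.02 (usual care) and 0.0174 (aspirin) per year; competing-death hazards 0.018 and 0.0185; recruitment 42 months, then 30 months of follow-up. The article does not name the accrual pattern. Uniform entry is assumed and tested first.

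**Step 1: reproduce the design.** With event hazard λ and competing hazard μ, the cumulative incidence is F(t) = λ/(λ+μ) × (1 − exp(−(λ+μ)t)).

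- F(5 years): 0.0911 usual care, 0.0796 aspirin. Both as stated.
- Subdistribution HR = ln(1−0.0796)/ln(1−0.0911), 0.8691 unrounded (stated 0.8692).
- Mean of F over follow-up of 2.5 to 6 years (uniform entry): 0.0782 and 0.0683, pooled 0.0732 (stated 0.0782, 0.0682, 0.0732).
- Events = 4(1.960+1.036)²/(ln 0.8692)² = 1828 after rounding up (stated 1827).

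Uniform entry over 42 months therefore returns the plan's own figures to within rounding.

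**Step 2: fix the cut.** 9 (set-up) + 27 (recruitment) + 9 (adjudication and report) = 45 months. This is the stated report date, so no follow-up beyond recruitment month 27 is left over.

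**Step 3: expected events at that cut.** Entered per arm: 12,605 × 27/42 = 8,103. Mean follow-up 1.125 years, maximum 2.25 years.

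- With competing risks, the mean of F over 0 to 2.25 years is 0.02187 (usual care) and 0.01906 (aspirin). Events: 8,103 × 0.02187 = 177 and 8,103 × 0.01906 = 154. Pooled about 331 to 332, or 18% of 1827.
- As a crude count, person-years per arm are 8,103 × 1.125 = 9,116. Events: 9,116 × 0.02 = 182 and 9,116 × 0.0174 = 159. Pooled 341, or 18.7% of 1827.

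**Step 4: compare.** Expected final control events are 12,605 × 0.0782 = about 985, and 226/985 = 22.9%. The 226 and the 23% are thus consistent with each other; the mismatch is with the 27-month cut. Against 226, an on-plan count is 1 − 182/226 = 19% to 1 − 177/226 = 22% lower. The stated figure lies (226−182)/√182 = 3.2 to (226−177)/√177 = 3.7 Poisson standard deviations above the on-plan expectation. Dividing the on-plan count by 226 would suggest a control rate of about 0.02 × 177/226 to 0.02 × 182/226, or 1.6% a year, when the true rate is 2%.

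**Step 5: what would give 226.**

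- A cut at 30 months: 218 control events with competing risks, 225 crude; 22.3% to 23.0% pooled.
- The 27-month cohort with 3 to 4 months of extra event capture: 216 to 229 with competing risks.
- Full accrual in 33 months (226 with competing risks) or 34 months (225 crude).

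A slow start moves the other way. With a linear 6-month ramp-up the crude control count is about 156, and with a 12-month ramp-up about 132.

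**The case against.** The strongest reply is that 226 is a parenthetical forecast of how much data the report will hold. What the article says will be judged is the event rate, and the anticipated control rate is 2% a year. A review based on events per person-year would read 2% in an on-plan trial whatever the parenthesis says. This stands. A reader might infer that 226 is a decision threshold, or that the error would lead to an unneeded extension. The documents support neither: they give the TSC an option and no numerical trigger.

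Second, the accrual curve is not stated for this forecast, and the full protocol may use another. This stands in part. Uniform entry is the pattern that reproduces the sample size, so a different curve for the review should be named. The abstract's average follow-up of 5 years, against 30 + 21 = 51 months (4.25 years) under uniform entry, might hint at earlier accrual. Taken literally with closure at month 72, it puts mean entry at month 12. Mean follow-up at month 27 would then be at least 15 months, giving at least 12,605 × 1.25 × 0.02 = 315 crude control events, which is also not 226.

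Third, a reader might conclude that the authors used a 30-month cut. That fits, but Step 5 shows it is not the only explanation.

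Fourth, the article allows review dates to move and cites the pandemic pause. How many events a pause would add depends on numbers recruited beforehand, which are not given. However, the stated month 45 is fully used by 9 + 27 + 9 and contains no pause.

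**Conclusion.** The forecast is wrong as written, at minor to moderate importance. At the stated cut the plan's assumptions give about 177 to 182 control events and 331 to 341 pooled, or 18-19% of 1827, in place of 226 and 23%. This rests on constant hazards, uniform entry over 42 months and an event cut at recruitment month 27. The first two reproduce the design figures, and the third follows from the timetable. Sample size, power, the 1827-event target and the primary analysis do not use the figure and are unaffected. The practical risk is limited to a raw-count reading of the review.

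A secondary point of wording: Estimation of vascular event rate contrasts the first phase of the pilot with "formal estimation of the control event rate, which will take place during the second phase", while the pilot ends at month 24 and the by-arm report comes at month 45. By then, on plan, 36/42 = 86% of the recruitment period has passed. If the second phase means something later than the pilot, the article should say so.

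**What to change.** - In both places, restate the expectation at 27 months of recruitment as about 177 to 182 control-arm and 331 to 341 pooled events (18-19% of 1827). Alternatively, keep 226 and 23% and state the cut date, event-capture window or accrual curve that produces them.
- State that the review compares events per person-year with the design rate: 2% a year in usual care for the DMEC, and about (2 + 1.74)/2 = 1.87% a year pooled for the TSC, which sees overall data only. The raw count then serves only to describe the information available.
- Reconcile the second-phase wording with the month-45 report.

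The cost is one recalculation and a few sentences in two sections. A pooled event projection at the review already scheduled after 24 months of recruitment would be a useful option but is not needed to correct the error.

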### Harms

The processes for reporting of SAE and ascertainment of outcome events will work in parallel. This is illustrated in Fig. 3.

**Fig. 3 Fig3:**
[figure not shown]
Ascertainment of serious adverse events and trial endpoints

The following events are exempted from expedited reporting using an SAE report form:
Events meeting the definition of SAE but which are listed as undesirable effects in the current Summary of Product Characteristics for aspirin (with the exception of hypersensitivity/allergic reactions which will subject to expedited reporting)Anything that constitutes a trial endpoint, as this will be assessed as part of the trialSAE which in the opinion of the Investigator are with reasonable probability unrelated to aspirin

Participating GP will be asked to contact the Regional Centres and provide details of potential SAE that are not excluded from expedited reporting as soon as they become aware of the event. Participants will be asked to contact the study site in the event of any emergency hospital admission. They will carry a Trial Participant ID card, which asks admitting hospitals to inform the Regional Centre of hospitalisations. Standard information will be collected and recorded on the CRF by the Regional Centre.

The Regional Centre will screen all potential SAE. Those not excluded will be recorded on an SAE report form. The Regional Principal Investigator will review causality, relatedness and expectedness, and forward the SAE report form to the Trial Coordinating Centre (as soon as possible and within 24 h of becoming aware of the event) who will notify the Chief Investigator. SAE identified in this way will be recorded and closely monitored until resolution and stabilisation or until it has been shown that the study medication or treatment is not the cause. Confirmed reports will be promptly forwarded unblinded to the Chair of the DMEC. All serious adverse events that fall or are suspected to fall within the criteria for a suspected unexpected serious adverse reaction (SUSAR) shall be treated as such until deemed otherwise. The event shall be reported immediately (within 24 h) of knowledge of its occurrence to the Chief Investigator. Safety information relating to adverse events not subject to expedited reporting that are captured as trial endpoints will be closely monitored by the DMEC throughout the trial.

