#### Secondary objectives

The secondary objectives of the research are:
(i)To assess the impact of the addition of low-dose aspirin to usual care in people with CKD and no CVD on the incidence of major intracranial and extracranial bleeds; this is hypothesised to be increased in those randomised to take aspirin. The key consideration in then whether the benefits of aspirin from the expected reduction in CVD events (primary objective) exceed the expected risks of major bleeding;(ii)To assess the impact of the addition of low-dose aspirin to usual care on other secondary and tertiary endpoints (all-cause mortality, combined endpoint of major vascular events and revascularisation [coronary and non-coronary], individual components of the primary endpoint, TIA, unplanned hospitalisation, hospitalisation for heart failure, new diagnosis of cancer [colorectal/other], death due to cancer [where cancer is the underlying cause of death], major non-traumatic lower limb amputation, CKD progression, health-related quality of life [HRQoL] and dementia);(iii)To examine a priori the effect of low-dose aspirin on primary, secondary and tertiary endpoints in various subgroups of people with CKD (high-risk and very high-risk CKD as defined by KDIGO on the basis of eGFR and UACR category), diabetes, age ≥ 70, eGFR < 45 mL/min/1.73 m^2^, UACR ≥3 mg/mmol, UACR > 30 mg/mmol);(iv)To assess the impact of the addition of low-dose aspirin to usual care in people with CKD and no CVD on the incidence of inpatient clinically relevant bleeds not meeting major bleeding criteria;(v)To assess the cost-utility of low-dose aspirin compared with usual care.

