#### Tertiary endpoints

Exploratory endpoints will be analysed as time to event from the date of randomisation through to the end of follow-up except hospitalisations, which will be reported as a rate over time.
Transient ischaemic attackUnplanned (emergency) hospitalisationsHospitalisation with heart failureNew diagnosis of cancer (colorectal/other)Death due to cancer (where cancer is the underlying cause of death)CKD progression (at least one of: > 30% fall in eGFR over 2 years [65]; need for renal replacement therapy or 50% decline in eGFR [66]; new eGFR< 15 mL/min/1.73 m^2^; 25% decline in GFR together with a drop in GFR category [3])New diagnosis of dementiaMajor non-traumatic lower limb amputation

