#### Follow-up assessments

There is no practice-based follow-up. Potential outcomes will be determined from a combination of routinely collected healthcare (GP and hospital) data, including death certification and cancer registration; reporting by GPs and admitting hospitals; and self-reporting by patients. All events identified as a potential cardiovascular endpoint or bleeding event requiring hospital admission will be formally adjudicated; outpatient sight-threatening eye bleeds will also be adjudicated.

The Regional Centres will regularly download a report from the ATTACK database to monitor if any trial participant does not have an eGFR reading recorded in their GP record in the previous 15 months. If this is the case, the GP Practice will be contacted to remind them of the NICE guideline to perform these tests annually as a minimum [56].

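### The unrestricted endpoint exemption from expedited SAE reporting conflicts with the hypersensitivity exception and the SUSAR rule for any reaction that is fatal or causes emergency admission

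*Protocol article*

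**What the plan says.** In the protocol article, under Methods: monitoring, Harms, the list opens with "The following events are exempted from expedited reporting using an SAE report form" and names three classes:

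- effects already listed in the aspirin product information, except hypersensitivity or allergic reactions, which are to be expedited;
- anything that "constitutes a trial endpoint, as this will be assessed as part of" the trial;
- events that the investigator considers probably unrelated to aspirin.

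GPs are asked to notify potential SAEs that are not excluded. Participants are asked to report any emergency admission, and their ID card asks hospitals to do the same. The Regional Centre screens all potential SAEs, and then: "Those not excluded will be recorded on an SAE report form". The Regional Principal Investigator reviews causality, relatedness and expectedness at that stage. A later sentence, opening "All serious adverse events that fall or are suspected to fall within the criteria for a suspected unexpected serious adverse reaction (SUSAR", requires such events to be treated as SUSARs and reported to the Chief Investigator within 24 hours. Exempted events that are captured as endpoints are to be monitored by the DMEC.

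Secondary objective (ii) names "endpoints (all-cause mortality, combined endpoint of major vascular events and revascularisation", and later in the same list "individual components of the primary endpoint, TIA, unplanned hospitalisation, hospitalisation for heart failure". The Secondary endpoints and Tertiary endpoints sections confirm death from any cause and unplanned (emergency) hospitalisation as endpoints.

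**The concern.** The second exemption has no qualifier. It is not confined to the primary outcome, to adjudicated events, or to vascular and bleeding events. Two of the trial's endpoints, death and unplanned admission, can result from almost any serious illness. Read as written, the exemption takes in reactions that the same section says must be expedited.

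What is at stake is patient safety and a workable rule. For a participant admitted as an emergency with a serious allergic reaction, one line tells staff to expedite and the next tells them not to. Someone who applies the endpoint line literally would complete no SAE form, and the causality and expectedness review described for such forms would not be triggered.

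**Working it through.** No arithmetic applies, and the plan gives no figure to reproduce. The check sets the exemption list in Harms beside the endpoint lists and the scope of adjudication. The article does not define an SAE, so the usual seriousness criteria are assumed (death, life-threatening, hospitalisation, disability, congenital anomaly, medically important).

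**Step 1: what the first and third exemptions leave to be expedited.** Two classes remain: (a) serious hypersensitivity or allergic reactions, and (b) serious events that are possibly related and not listed for aspirin.

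**Step 2: apply the second exemption and the SUSAR sentence.**

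| Event | Other rule in Harms | Second exemption | SUSAR sentence | Result |
|---|---|---|---|---|
| (a) fatal or admitted as an emergency | Expedite (exception within the first exemption) | Exempt | Would not normally apply, because the effect is listed | Direct conflict, with no other rule to resolve it |
| (b) fatal or admitted as an emergency | None exempts it | Exempt | Report within 24 hours | Direct conflict between two rules |
| (a) or (b), with no death, emergency admission or other endpoint | None exempts it | Does not apply | Applies to (b) | Reportable, no conflict |
| Judged unrelated | Exempt (third exemption) | Makes no difference | Does not apply | Exempt in any case |

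The exception for hypersensitivity is attached only to the first exemption. Nothing says that it overrides the second.

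**Step 3: the order of the steps.** GP notification covers only events that are not excluded. The SAE form, and with it the review of causality and expectedness, follows exclusion. Screening must involve some view on listing and relatedness, because the first and third exemptions depend on them. But an event that meets the second exemption can be set aside without either. The step that would recognise a SUSAR is therefore described downstream of the step that may remove it.

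**Step 4: the reason given for the exemption.** Endpoints are exempt because the trial will assess them. Follow-up assessments states the scope: "All events identified as a potential cardiovascular endpoint or bleeding event requiring hospital admission will be formally adjudicated". Outpatient sight-threatening eye bleeds are added. Tertiary endpoints says that events are analysed as time to event, "except hospitalisations, which will be reported as a rate over time". So an admission or death that is neither cardiovascular nor a bleed is counted in the analysis, but no adjudication of the individual case is described for it. The reason holds for adjudicated endpoints and fails for the two broad ones.

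**The case against.** The case for the current text is substantial. The SUSAR sentence has no endpoint exception, so unexpected related reactions are still required to be reported within 24 hours. The hypersensitivity rule is a specific positive instruction, and its intent is clear. Asking for notice of every emergency admission and screening all potential SAEs would have little purpose if every admission were exempt. A sensible reader may take the diagnosis, such as anaphylaxis, to be the event, and admission or death to be only its outcome. The DMEC monitors exempted endpoint events, and the pilot safety review uses reports from participants and professionals as well as other SAEs. Fig. 3, the endpoint appendix and the full protocol are not shown and may define the exemption more narrowly.

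Most of this stands, and it limits the point. A reader might infer that nearly every reaction meant for expedited reporting is exempt, or that the 24-hour route would receive almost nothing. The documents do not support that, because of the SUSAR sentence and the direct notification of admissions. Nor would a count of deaths from the other-cause rates in the sample-size section measure the problem. Those are deaths, not reactions, and any judged unrelated are exempt under the third line anyway.

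The objection does not remove the conflict. Intent has to be inferred because precedence is not stated, the SUSAR sentence does not normally reach listed allergic reactions, and DMEC monitoring is not 24-hour reporting of a case.

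**Conclusion.** The point holds as a contradiction within the Harms section. For a serious reaction that is fatal or causes emergency admission, the endpoint exemption opposes the hypersensitivity exception and the SUSAR sentence, and the text does not say which prevails. The conflict is sharpest for hypersensitivity, which the SUSAR rule would not normally recover.

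Its size cannot be given. The documents report no expected rate of hypersensitivity or of unlisted related reactions, and no split of SAEs by seriousness criterion. The conclusion rests on three assumptions: the usual SAE criteria, treatment of a listed effect as expected, and Fig. 3 and the full protocol not already restricting the exemption. The objection is to a rule that is stated, not to detail left out of a condensed article. The change should be made because it concerns safety reporting and costs little.

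**What to change.** Reconcile the rules in the Harms section.

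1. Limit the second exemption to endpoints that are individually adjudicated, that is, potential cardiovascular and bleeding endpoints. As a minimum, state that death from any cause and unplanned hospitalisation are not in themselves grounds for exemption. The other tertiary endpoints need not be taken out of the exemption.
2. State that the hypersensitivity exception and the SUSAR check take precedence over all exemptions and are applied before any of them.
3. Bring Fig. 3 and the Regional Centre screening instructions into line, if they do not already say this.

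The cost is a short text amendment, an updated screening procedure, and some additional screening and SAE forms. The extra forms are limited because events judged unrelated stay exempt under the third line. The documents give no basis for estimating their number.
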